**Methods:**

An investigator-initiated, prospective, multicenter, open-label, noninferiority, cluster-randomized controlled clinical trial is being implemented under the auspices of the national TB control program in China. Close contacts of school pulmonary TB index cases, regardless of diagnostic type, are actively screened for symptoms using interferon-gamma release assays, chest imaging, and sputum molecular diagnostic testing to detect TB infection and exclude active TB. Eligible latent TB infection cases will be randomized in a 1:1 cluster ratio to receive either the standard 3HR regimen or the novel ultrashort 1H_3_P_3_ regimen for TPT, with subsequent follow-up for up to 2 years to assess disease progression. The primary composite end point includes microbiologically confirmed TB (sputum culture or molecular diagnostic testing) or clinically diagnosed TB. With 80% power to detect noninferiority (20% margin), the study requires 1760 participants per arm, accounting for cluster design effects.

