### Study Objectives and End points

The primary objective is to demonstrate noninferiority of the ultrashort course of the 1H_3_P_3_ TPT regimen compared with the standard 3HR regimen in preventing active TB, as measured by the 24-month cumulative incidence of active TB following randomization. The secondary objectives include: (1) to compare safety, patient-reported quality of life, and treatment discontinuation rates attributable to AEs between the regimens; (2) to evaluate treatment adherence using protocol-defined completion criteria; (3) to assess acquired *M tuberculosis* drug resistance among participants who develop active TB after TPT; and (4) to establish a contemporary nonintervention cohort for exploratory comparison, delineating the natural progression to active TB among individuals with high-risk LTBI in whom active TB has been ruled out.

The primary end point is a composite of bacteriologically confirmed or clinically diagnosed active TB within 24 months after randomization. Bacteriologically confirmed active TB refers to *M tuberculosis* identification via ≥1 sputum culture and/or molecular assay (eg, GeneXpert MTB-RIF) with detectable bacterial load. Clinically diagnosed TB combines objective clinical symptoms (≥2 of the following: cough ≥2 weeks, fever, night sweats, weight loss >10%, or hemoptysis) and imaging findings highly suggestive of active TB (eg, cavity or nodular lesions on chest CT), after exclusion of alternative diagnoses. Secondary end points include severity-graded AEs, treatment discontinuation (defined as any permanent cessation prior to regimen completion), treatment completion (defined as completing ≥90% of scheduled doses within 110% of the planned treatment duration), all-cause mortality, and acquired drug resistance determined by drug susceptibility testing or targeted molecular assays of *M tuberculosis* isolates from active TB cases. Exploratory analysis will use the nonintervention cohort to establish the background incidence of active TB, against which the risk reduction of each TPT regimen can be calculated. Patient-reported outcomes (PROs) will be calculated using health state utility values and EuroQol visual analog scale scores.

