### Randomization and Sample Size Calculation

Enrolled LTBI participants linked to the same index case will be defined as a cluster [14,15], with an assumed average cluster size of 4 participants. Cluster-level randomization will be triggered when ≥1 eligible participant is enrolled within a cluster. Randomization sequences will be pregenerated by the study statistician using SAS (version 9.4; SAS Institute Inc) and will not be accessible to any personnel involved in enrollment, assignment, or intervention delivery. Designated personnel will perform centralized randomization via the interactive web response system. Randomization results will be relayed to the respective site investigators. This is an open-label study, and all participants within the same cluster will receive identical group assignments. To address intercenter heterogeneity, a 2-stage randomization strategy will be applied: in the first stage, stratification by study site will balance baseline characteristics across centers; in the second stage, permuted block randomization (block size=4) within each site will ensure immediate group balance during participant enrollment.

On the basis of surveillance data from China’s National Tuberculosis Control Program, we estimate that the 2-year cumulative active TB incidence among LTBI participants will be 7% [16,17]. Both the 3HR and 1H_3_P_3_ regimens are assumed to have 70% protective efficacy (ie, reducing the 2-year cumulative incidence of active TB into 2.1%).

The intracluster correlation coefficient (ICC) was incorporated into calculations. A systematic review reported ICC values of 0.028 (range 0.0005‐0.21) for school-based clusters [15], while the National Institutes of Health Pragmatic Trials Collaboratory suggested a range of 0.01 to 0.05 [18]. Therefore, we adopted a conservative ICC estimate of 0.05 for this study.

Using these parameters and a prespecified noninferiority margin of a 20% relative reduction in protective efficacy, a total of 396 clusters (n=1584 participants) per treatment arm are required to achieve 80% power at a 1-sided *α*=.05. This sample size is calculated to satisfy the clinically meaningful noninferiority margin, accounting for the cluster randomized design (ICC=0.05, average cluster size=4). Accounting for a 10% attrition rate to mitigate the impact of loss to follow-up on statistical power and outcome validity, each arm will enroll 1760 participants.

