### Statistical Analysis

Statistical analyses will be performed using SAS and R (R Foundation for Statistical Computing). Multiple imputation will be conducted to handle missing data, with additional inverse probability weighting applied for the nonintervention cohort to adjust for potential attrition bias. Continuous variables will be summarized as mean (SD) or median (IQR), as appropriate. Categorical variables will be summarized as counts and percentages.

The primary analysis will assess the noninferiority of the 1H_3_P_3_ regimen compared to the 3HR regimen in preventing active TB over the 24-month follow-up period, and the primary end point is the composite of bacteriologically confirmed or clinically diagnosed active TB. To account for the cluster randomized design and the inherent correlation within clusters, we will use a Cox proportional hazards regression model with shared frailty terms and exact likelihood estimation. Noninferiority of the 1H_3_P_3_ regimen relative to the 3HR regimen will be concluded if the analysis demonstrates that the 1H_3_P_3_ regimen does not experience a ≥20% relative reduction in protective efficacy for preventing active TB over the 24-month follow-up period. To enhance precision and address potential baseline imbalances despite randomization, the model will adjust for key prespecified covariates, such as age, sex, BMI, characteristics of the index case (smear or cavitation status), and cluster size. Outcomes will be assessed via 2 prespecified analyses with explicit definitions: the modified intention-to-treat population includes all randomized participants who received at least 1 dose of the study medication, analyzed by the assigned treatment group regardless of subsequent protocol deviations or treatment discontinuation; the per-protocol population includes all randomized participants who completed ≥90% of scheduled doses within 110% of the planned treatment duration without major protocol deviations (including use of prohibited concomitant anti-TB medications, enrollment despite exclusion criteria, or unblinding to outcome assessors). Prespecified subgroup analyses will examine treatment effect heterogeneity by age (13-17 years vs ≥18 years) and index case features (smear or cavitation status), tested through interaction terms in Cox models (interaction *P*<.10).

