For secondary end points, all AEs, serious AEs (SAEs), and treatment discontinuations due to AEs will be documented. Group differences in AE proportions will be analyzed using the chi-square test or Fisher exact test (2-sided *α*=.05). Treatment completion is defined as consuming ≥90% of planned doses within 110% of the planned treatment duration (≥11 doses within 6 weeks for the 1H_3_P_3_ group and ≥81 doses within 16 weeks for the 3HR group). The 2-year cumulative incidence of active TB in the nonintervention cohort will be calculated using the Kaplan-Meier method, with 95% CI estimated. The protective efficacy of the 1H_3_P_3_ and 3HR regimens relative to the nonintervention cohort will be quantified as the risk reduction rate: 1–(intervention group incidence/nonintervention group incidence). The Fisher exact test will be used to compare incidence differences among the 3 cohorts.

All analyses concerning the PRO end point will be explicitly restricted to the subgroup of participants who complete the EuroQol 5-Dimensions 3-level questionnaire. The baseline characteristics of this PRO subgroup will be compared between the 2 arms to confirm that randomization balance was maintained. Any interpretation of PRO findings will explicitly acknowledge their exploratory nature and the fact that they are derived from a subset of the total study population. Trends in PRO metrics over time will be visualized using line graphs, with mean values and 95% CIs plotted to illustrate group-level changes. A mixed-effects model for repeated measures will be used to compare PRO differences between the 1H_3_P_3_ and 3HR groups across time points, with fixed effects including treatment group, assessment time point, treatment group×time point interaction, age, sex, BMI, and index case cavitation status, and a random participant-specific intercept to account for within-subject correlation from repeated assessments.

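### The noninferiority limit is given in protective efficacy, with no number on the scale of the primary Cox model, and the wording and the sample size imply different limits (HR about 1.47 and about 1.68)

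*Protocol article*

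**What the plan says.** All places are in the protocol article.

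- **Objective** (Study Objectives and End points): noninferiority in preventing active TB, "as measured by the 24-month cumulative incidence of active TB following randomization".
- **Primary model** (Statistical Analysis): "we will use a Cox proportional hazards regression model with shared frailty terms and exact likelihood estimation". The comparison is 1H3P3 against 3HR.
- **Decision rule** (same paragraph): noninferiority is concluded if 1H3P3 "does not experience a ≥20% relative reduction in protective efficacy for preventing active TB over the 24-month follow-up period". No hazard ratio, risk ratio or risk difference is attached.
- **Planning values** (Randomization and Sample Size Calculation): untreated two-year incidence 7%, efficacy 70% in both arms, hence 2.1% in each. The margin is again described as a 20% relative loss of efficacy. The ICC is 0.05 and the mean cluster size 4. The section states that 396 clusters (1584 participants) per arm "are required to achieve 80% power at a 1-sided *α*=.05", and 1760 per arm after 10% attrition.
- **Abstract, Methods**: "With 80% power to detect noninferiority (20% margin), the study requires 1760 participants per arm". It does not say what the 20% is a percentage of.
- **Discussion**: the margin is justified from the same 7% and 2.1%.
- **Secondary analyses** (Statistical Analysis): efficacy of each regimen "relative to the nonintervention cohort will be quantified as the risk reduction rate". Study Objectives and End points describes that comparison as exploratory.

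**The concern.** Efficacy is a comparison with no treatment. A Cox model of two treated arms has no untreated risk in it, so its hazard ratio cannot be set against the printed rule until someone supplies that risk and converts. The article does not say which risk to use or what limit results. Its planning values allow a conversion, but the sample size points to a different margin from the one in the text.

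The confirmatory decision is at stake. If the number is chosen after data are available in an open-label trial, one result could be declared noninferior or not according to the conversion used. The stated 80% power also belongs to only one of the possible tests.

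**Working it through.** **Inputs.** Risk 2.1% in both arms, untreated risk 7%, one-sided alpha 0.05 (z = 1.645), power 80% (z = 0.842), ICC 0.05 and cluster size 4, all from Randomization and Sample Size Calculation. Design effect = 1 + (4 − 1) × 0.05 = 1.15.

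**1. Reproducing the plan's figure.** Take 20 percentage points of efficacy (70% to 50%). Risk at the margin is 7% × 0.50 = 3.5%, and the margin is 3.5% − 2.1% = 1.4 points. The Farrington-Manning test for a risk difference uses n = [z_α√V0 + z_β√V1]² / d² per arm.

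- V0 is the variance under the null. The restricted estimates are 3.008% and 1.608%, so V0 = 0.04499.
- V1 = 2 × 0.021 × 0.979 = 0.04112.
- n = [1.645√0.04499 + 0.842√0.04112]² / 0.014² = 1377.2.
- 1377.2 × 1.15 = 1583.8, or 395.96 clusters. This rounds to 396 clusters, 1584 participants, and 1584/0.9 = 1760.

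The match is exact. Other routes miss:

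| Calculation (one-sided 0.05, design effect included) | Per arm |
|---|---|
| Risk difference 1.4 points, unpooled variance | 1493 |
| Risk difference 0.98 points, unpooled / Farrington-Manning | 3044 / 3141 |
| Hazard- or risk-ratio sizing at HR 1.68 (RR 1.67), several formulas | 1893 to 2637 |
| Hazard- or risk-ratio sizing at HR 1.47, several formulas | 3647 to 4616 |

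**2. The limit implied by the wording.** 70% × 0.8 = 56% efficacy. Risk at the margin is 7% × 0.44 = 3.08%, so the difference is 0.98 points. HR = ln(1 − 0.0308)/ln(1 − 0.021) = 1.474 (risk ratio 3.08/2.1 = 1.467).

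**3. The limit implied by the sizing.** HR = ln(1 − 0.035)/ln(1 − 0.021) = 1.679 (risk ratio 3.5/2.1 = 1.667).

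**4. What happens if the planning assumptions come true.** With 1584 evaluable per arm, there are 2 × 1584 × 0.021 = 66.5 events, or 66.5/1.15 = 57.85 effective events.

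- SE of log HR = √(4/57.85) = 0.263. Upper bound = exp(1.645 × 0.263) = 1.54.
- Effective n per arm = 1584/1.15 = 1377.4. SE of the risk difference = √(0.04112/1377.4) = 0.546 points. Upper bound = 1.645 × 0.546 = 0.90 points.

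| Limit applied | Upper bound | Result |
|---|---|---|
| HR 1.47 | 1.54 | fails |
| 0.98 points | 0.90 points | passes |
| HR 1.68 | 1.54 | passes |
| 1.4 points | 0.90 points | passes |

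**5. Power at 1584 per arm.** For a hazard ratio, power = Φ(ln(HR limit)/0.263 − 1.645). For the risk difference, the Farrington-Manning formula in step 1 is solved for power.

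| Test | Power |
|---|---|
| Risk difference 1.4 points | 80% |
| HR 1.68 (same margin, ratio scale) | Φ(0.518/0.263 − 1.645) = 63% |
| Risk difference 0.98 points | 54% |
| HR 1.47 (same margin, ratio scale) | Φ(0.388/0.263 − 1.645) = 43% |

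Moving from difference to ratio costs 80% to 63% at the sizing margin. The drop from 80% to 54% comes from the margin alone: relative wording against percentage points.

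**The case against.** The fairest reply is that the margin is anchored. The sample size section and the Discussion both state efficacy through 7% and 2.1%, so a reader can derive 3.08% against 2.1% and an HR of about 1.47. That stands, and it means the rule is not beyond interpretation. It does not close the gap, because the rule does not say those risks are fixed and the sample size was evidently computed with a wider margin.

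Three stronger readings are tempting, and the document does not support them:

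- *The nonrandomised decliner cohort will enter the primary decision.* Efficacy is calculated against that cohort only among the secondary analyses, and the objectives label the comparison exploratory. Nothing assigns it to the primary test.
- *The limit could lie anywhere from about HR 1.2 to 2.8.* That spread comes from (1 − 0.8 × PE)/(1 − PE) with 3HR efficacy (PE) set anywhere from 50% to 90%. Only 70% is in the document. The ambiguity the document itself creates is 1.47 against 1.68, together with the choice of scale.
- *There is no confidence criterion.* A one-sided alpha of .05 is stated, and writing out the matching bound is detail that an article may leave to the analysis plan.

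It is also true that at risks near 2% the hazard ratio and risk ratio almost coincide (1.474 and 1.467), so a Cox model for a cumulative-incidence objective is not in itself a problem. What matters is the difference scale against the ratio scale. An unseen analysis plan may contain a numeric limit, but the printed margin and sample size would still disagree.

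**Conclusion.** The point holds and needs correcting before analysis. The printed rule cannot be applied to the printed model without a conversion that the article does not fix. The wording (0.98 points, HR about 1.47) and the sample size (1.4 points, HR about 1.68) support different limits. With identical arms at the planned 2.1%, the verdict depends on which is used. The stated 80% power holds only for the 1.4-point risk difference. The alternatives have about 63%, 54% and 43%.

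This rests on two assumptions. Risk-difference sizing is inferred from an exact numerical match and from the failure of the other formulas tried; the article does not state it. The bounds and powers are approximate: a design effect of 1.15 stands in for the frailty model, covariate adjustment is ignored, and 1584 per arm are taken as evaluable.

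**What to change.** Before database lock:

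1. Reconcile whether the 20% is a relative loss (70% to 56%) or percentage points of efficacy (70% to 50%), and use the same wording in the Abstract, the sample size section, the Statistical Analysis section and the Discussion.
2. State one numeric limit on the scale of the primary test, derived from the fixed 7% and 2.1% and not from the nonintervention cohort. Name the upper one-sided 95% confidence bound as the criterion. Either of two forms will do: an HR limit for the Cox model, or a 24-month risk-difference limit with cluster-robust inference and the Cox HR supportive. The second matches the objective and the apparent sizing.
3. Restate the power for that test.

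The text change is small, but its consequence is not. Power at the planned size falls below 80% unless the 1.4-point risk difference is the test. In that case the relative wording has to be corrected and the HR becomes secondary. Keeping the relative margin at 80% power would need about 3,141 evaluable per arm on the risk difference. On the hazard ratio it would need about 4,500: 164.3 effective events / (2 × 0.021) × 1.15 = 4,498. The planned number is 1584. The Results section expects recruitment to continue until September 2026, so the decision is best taken now.

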## Methods

### Study Design

This is a multicenter, prospective, cluster randomized, noninferiority clinical trial comparing the protective efficacy and safety of the 1H_3_P_3_ regimen with those of the 3HR regimen for TPT in adolescents and adults with LTBI. Prior to trial initiation, close contacts of pulmonary TB index cases within school environments will undergo active screening through the TB-YOUTH Screening program, a cross-sectional study (ClinicalTrials.gov NCT06033807), under the auspices of the National Tuberculosis Control Program in China. After excluding active TB, eligible LTBI participants will be grouped into clusters by their corresponding index cases. The clusters will then be randomized in a 1:1 ratio to receive either the 1H_3_P_3_ or the 3HR regimen for TPT. Medication adherence and adverse events (AEs) will be monitored at week 2, month 1, and month 2 for the 1H_3_P_3_ group, and at week 2 and then monthly until month 4 for the 3HR group after treatment initiation. Participants will undergo follow-up clinical assessments every 6 months for 2 years following randomization. The preventive efficacy of each study arm against active TB will be evaluated at the conclusion of the follow-up period.

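### If contacts can join a cluster after open allocation, the enrolled cluster size in the primary Cox model is not a baseline covariate and can bias the hazard ratio in either direction

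*Protocol article*

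**What the plan says.** All references are to the protocol article.

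- **Statistical Analysis.** The primary analysis is a "Cox proportional hazards regression model with shared frailty terms and exact likelihood estimation". The reason given for covariates is: "To enhance precision and address potential baseline imbalances despite randomization, the model will adjust for key prespecified covariates". The list gives age, sex and BMI and ends with "characteristics of the index case (smear or cavitation status), and cluster size". It does not say when cluster size is counted.
- **Randomization and Sample Size Calculation.** On what a cluster is: "Enrolled LTBI participants linked to the same index case will be defined as a cluster". On when it is randomized: "Cluster-level randomization will be triggered when ≥1 eligible participant is enrolled within a cluster". On who learns the result: "Randomization results will be relayed to the respective site investigators". On blinding: "This is an open-label study, and all participants within the same cluster will receive identical group assignments". Nothing closes a cluster to new members at that point.
- **Study Design.** Eligible participants are first grouped by index case, and then: "The clusters will then be randomized in a 1:1 ratio to receive either" of the two regimens. TPT Intervention also describes participants already clustered when they are randomized. Table 2 places screening and consent in the 30 days before allocation at day 0.

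**The concern.** A covariate used to correct baseline imbalance has to be fixed before allocation. Under the wording of the randomization section, a cluster could be randomized on its first member. The remaining contacts would then accept or decline knowing whether they face 12 or 90 doses, and the final enrolled size would partly be an effect of the arm.

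The number of infected contacts around an index case plausibly reflects infection pressure and so predicts TB. Suppose fewer contacts accept 3HR. A 3HR cluster with a given number enrolled then comes from a larger infected group than a 1H3P3 cluster with the same number enrolled. Comparing arms at equal enrolled size sets higher-risk 3HR clusters against lower-risk 1H3P3 clusters, and the hazard ratio moves down, toward noninferiority. If 3HR attracts more joiners, it moves up. In either case the primary conclusion would depend partly on a covariate that was meant to protect it.

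**Working it through.** **1. Order of events.** The randomization section (trigger at one enrolled member, no closing rule) permits joining after allocation. Study Design, TPT Intervention and Table 2 suggest that grouping and consent come first. No sentence states outright that members join later, and none rules it out. The rest is therefore conditional on late joining.

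**2. Figures from the article.**
- Incidence is 7% untreated and 2.1% on either regimen (70% efficacy).
- Margin: a 20% relative loss of efficacy gives 0.8 × 70% = 56%. Incidence at the margin is 7% × (1 − 0.56) = 3.08%, and the ratio is 3.08/2.1 = 1.467.
- Planned size: 396 × 4 = 1584 per arm, taken as stated. Design effect: 1 + (4 − 1) × 0.05 = 1.15.
- Enrolled per index case to December 2025: 2478/627 = 3.95.

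The article gives no uptake by arm and no relation between cluster size and risk, so both are assumed below.

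**3. Assumed model.** Eligible contacts E = 1 + negative binomial with mean 4, so the mean is 5 (dispersion 1, 2 and 4 tried). Enrolled n = 1 + Binomial(E − 1, uptake in the arm). TB rate is proportional to E^b, and the true hazard ratio is 1. A Poisson model with arm and n (or log n) stands in for the Cox model, since events are rare. It is evaluated by exact enumeration, without smear/cavitation or frailty terms. Mean enrolled size is 1 + 4 × 0.9 = 4.6 at 90% uptake and 1 + 4 × 0.7 = 3.8 at 70%.

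**4. Rough hand check.** With 4 enrolled, the pool is about 1 + 3/0.9 = 4.33 for 1H3P3 and 1 + 3/0.7 = 5.29 for 3HR. At b = 0.5 the spurious ratio is about (4.33/5.29)^0.5 = 0.90, close to the enumerated value below.

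**5. Error rate at the margin.** Effective events are 0.021 × 1584/1.15 = 28.9 and 0.0308 × 1584/1.15 = 42.4. SE = √(1/28.9 + 1/42.4) = 0.241. One-sided error = Φ(−1.645 − ln(adjusted HR)/SE). For 0.92: −1.645 + 0.083/0.241 = −1.30, which gives about 10%.

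| Uptake 1H3P3 vs 3HR | b | Adjusted HR (true 1) | One-sided error |
|---|---|---|---|
| 90% vs 90% | 0.5 | 1.00 | 5% |
| 75% vs 70% | 0.5 | about 0.98 | about 6% |
| 80% vs 70% | 0.5 | about 0.96 | about 7% |
| 90% vs 70% | 0.25 | about 0.96 | about 7% |
| 90% vs 70% | 0.5 | about 0.92 | about 10% |
| 90% vs 70% | 1.0 | 0.83 to 0.85 | 16% to 20% |
| 70% vs 90% | 0.5 | about 1.09 | about 2% |

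At 90% vs 70%, using E instead of n gives 1.00 to 1.01 and about 5%. Omitting size gives 1.00 to 1.03 and 4% to 5%.

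**6. Second model.** Here a latent infectiousness drives both contact numbers and risk, and the analysis adjusts for a smear/cavitation marker. True HR is 1.467, with 396 clusters per arm and 800 simulated trials. Risk rises by 0.5 on the log scale per SD of infectiousness. With uptake 70% vs 60%, adjusting for enrolled size gives HR 1.36 and 10.8% error, against 1.46 and 4.8% without size. Equal uptake gives 5.2% error. Uptake of 50% vs 80% reverses the bias (HR 1.80, error 0.5%). If size is unrelated to risk, there is no bias.

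**The case against.** **The premise is inferred.** The one-participant trigger may only mean that a single-person cluster can be randomized. If grouping and consent always precede allocation, enrolled size is a proper baseline covariate. This stands: the article supports a conflict about the sequence, not a finding that clusters grow.

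**The covariate list is illustrative, and its stated purpose points to a baseline count.** A fuller plan may define it so. This stands in part. As printed, though, the cluster is defined by enrolment and has no closing rule, so the article's own definition allows the wrong count.

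**The direction is not established.** A reader might infer that the primary model is biased toward noninferiority. The article does not support that: it reports no uptake by arm and no relation between size and risk. Its remarks on poor 3HR adherence in China and on the acceptability of the short regimen make higher 1H3P3 uptake plausible, no more. Opposite uptake reverses the bias.

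**The sizes rest on assumptions.** Small uptake gaps give small effects, and smear/cavitation adjustment could absorb some of the bias. In the second model it did not absorb all of it. Frailty was not simulated. It is not expected to remove the bias, because frailty is assumed independent of the covariates.

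**The deeper issue would be recruitment after open allocation.** This is correct. Changing the covariate does not cure selective joining by individual risk, which is a separate problem.

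**Conclusion.** The point holds conditionally. The article leaves open whether a cluster can grow after its arm is known, and it lists enrolled cluster size as a baseline adjustment in the primary model. Three conditions must all hold for bias: late joining, uptake that differs by arm, and contact numbers that predict TB beyond the other covariates. If they hold and 1H3P3 attracts more joiners, the illustration puts the adjusted hazard ratio at about 0.83 to 0.98 instead of 1, with one-sided error of about 6% to 20% instead of 5%. If 3HR attracts more, the example gives about 1.09 and 2%, which costs power. Equal uptake gives no bias. The uptake rates, the mean of 5 eligible contacts and the exponents are assumptions, not trial data.

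**What to change.** 1. In Statistical Analysis, replace cluster size with the number of LTBI-positive or eligible contacts of the index case recorded before the cluster is randomized, provided screening recorded it for every cluster. The article places screening ahead of the trial, but it does not say that a complete count exists at randomization, so this must be checked.
2. If the count is not available for all clusters, drop cluster size from the primary model.
3. Report enrolled cluster size by arm as a check on differential uptake.
4. Reconcile Study Design, TPT Intervention, Table 2 and the randomization section on whether members may join after allocation. If they never do, saying so settles the matter and enrolled size may stay.

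The cost is a line or two of text, plus retrieval of the count from the screening study. A count taken before allocation may explain slightly less variance. The change remains possible although 2478 participants were enrolled by December 2025, because analysis follows the 2-year follow-up. It removes only the bias due to the covariate.
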